### 2.7 Care for intervention group

The intervention group will undergo a six-month program including education sessions, training sessions, and harmonica sessions. Training and harmonica sessions will be conducted in person at the hospital, followed by daily home-based exercises with continuous tele-supervision and feedback delivered via WeChat. Details are listed in Table 1.

**Table 1 T1:** Components of the care for the intervention and control groups.

**Components**	**Contents**	**In-hospital/home-training**	**Time point**	**Intervention group**	**Control group**
**Education sessions**					
Self-management strategies	COPD self-management knowledge: 1. The pathophysiology, symptoms, progression, and risk factors of COPD 2. Recognizing and avoiding triggers, the importance of regular physical activity 3. Adhering to prescribed medication regimens, using oxygen therapy correctly 4. Lifestyle modifications: smoking cessation, healthy diet, and stress management	In-hospital	T0	√	√
Inhaler techniques	Correct usage protocols for pressurized metered-dose, dry powder inhaler, soft mist inhaler. Daily storage and cleaning of inhalation devices, and measures to prevent adverse reactions	In-hospital	T1	√	√
Airway clearance methods	Airway clearance techniques: 1. The ACBT techniques 2. Postural drainage 3. The OPEP techniques	In-hospital	T2	√	√
**Training**					
Pursed-lip and diaphragmatic breathing	Steps for pursed-lip abdominal breathing: 1. Positioning: Adopt a comfortable position, whether sitting, standing, or lying down 2. Hand Placement: Place one hand on the abdomen and the other on the chest to help monitor the movement of the diaphragm and chest respectively 3. Inhalation: Close the mouth and inhale through the nose. During inhalation, allow the abdomen to expand gently. The hand placed on the abdomen should move outward, while the hand on the chest should remain relatively stationary or move minimally 4. Exhalation: • Purse the lips as if whistling or making an “s-s-s” sound • Exhale slowly through the pursed lips, allowing the abdomen to contract • The hand on the abdomen should move inward during exhalation • The exhalation should be twice as long as the inhalation to ensure effective lung emptying Frequency: 30 times/set, 15 min/day, 5 days/week	In-hospital and home-training	T0 to T3	√	√
Air cycling exercise	Steps for air cycling exercise: 1. Lie supine on the bed with the lumbar and dorsal regions closely adhering to the mattress, placing the hands on both sides of the body 2. Adjust the breathing, then lift both legs and slowly perform a pedaling motion as if cycling 3. Maintain natural respiration throughout the training process and avoid breath-holding. Allow for intermittent rest periods of 10–30 s as needed Frequency: 30 cycles (per leg)/set, 3 sets/day, 5 days/week	In-hospital and home-training	T0 to T3	√	√
Hip bridge exercise	Steps for hip bridge exercise: 1. Lie supine on the bed with the hands placed on both sides of the body 2. Bend the knees and firmly plant the feet on the bed surface, flexing the knee joints to a 90-degree angle 3. Adjust the breathing. During exhalation, contract the abdominal muscles and simultaneously use the gluteal muscles to lift the hips upward, aligning the knees, hips, and shoulders into a straight line 4. Maintain this position for 5–10 s with the abdomen and glutes tightened, while continuing to breathe naturally and avoiding breath-hold in 5. Upon exhaling again, lower the hips back to the bed surface Frequency: 10 repetitions/set, 3 sets/day, 5 days/week	In-hospital and home-training	T0 to T3	√	√
Seated stretching	Steps for seated stretching: 1. Sit upright on a chair with a resistance band looped around a fixed post 2. Grasp each end of the resistance band with the hands, wrapping it around the palms 1 to 2 times. Keep the elbows close to the sides of the body 3. After adjusting the breathing, exhale while pulling the resistance band backward to its maximum range of motion 4. Hold the position briefly, then slowly return to the starting position Frequency: Each movement 10 times/set, 3 sets/day, 5 days/week	In-hospital and home-training	T0 to T3	√	√
Standing stretching	Steps for seated stretching: 1. Stand with feet and hands apart, chest lifted and abdomen tucked in 2. Loop a resistance band around the back and grasp it with both hands, wrapping it around the palms 1 to 2 times 3. Stabilize the scapulae, bend the arms, and place the elbows close to the sides of the body 4. During exhalation, use the force from the chest wall to push the resistance band forward, leading with the arms 5. Hold the position briefly, then slowly return to the starting position Frequency: Each movement 10 times/set, 3 sets/day, 5 days/week	In-hospital and home-training	T0 to T3	√	√
Lower limb stretching	Steps for lower limb stretching: 1. Fold the elastic band in half and loop it around the middle of one foot, passing through the arch. Place the other foot firmly on the elastic band, with the legs slightly apart 2. Hold the elastic band with one hand, wrapping it around the palm 1 to 2 times, and use the other hand to steady oneself against a chair back or tabletop to maintain body stability 3. During exhalation, engage the thigh muscle of the leg with the elastic band to lift the knee upward, resisting the band's tension and raising it as high as possible. As inhalation occurs, slowly lower the leg 4. Switch legs and repeat the above movements Frequency: Each movement 10 times/set, 3 sets/day, 5 days/week	In-hospital and home-training	T0 to T3	√	√
**Harmonica sessions**					
Instrument anatomy	Covers harmonica components—comb, reed plates, mouthpiece—and note arrangement	In-hospital	T0	√	
Maintenance and cleaning	1. Clean regularly: Use warm water and a mild soap to gently wash the harmonica. Avoid using harsh chemicals or hot water 2. Dry thoroughly: Make sure all parts are completely dry before reassembling to prevent reeds from sticking 3. Store properly: Keep the harmonica in a dry, cool place to maintain its condition	In-hospital	T0	√	
Harmonica-based breathing techniques	1. Inhale slowly and deeply using the diaphragm 2. Exhale in a controlled manner, similar to pursed-lip breathing, ensuring steady airflow and clear sound	In-hospital	T0	√	
Hands-on harmonica repertoire teaching	Instructors will select songs of gradually increasing difficulty, providing hands-on teaching for each song and offering personalized guidance. Frequency (home-training): 30 min (no-break)/day, 5 days/week	In-hospital and home-training	T0 to T3	√	

COPD, Chronic Obstructive Pulmonary Disease; ACBT, Active Cycle of Breathing Technique; OPEP, Oscillating Positive Expiratory Pressure; T0, baseline; T1, 1 month post-baseline; T2, 3 months post-baseline; T3, 6 months post-baseline.

#### 2.7.1 Education sessions

The intervention group will participate in three sequential 45-min educational sessions designed to enhance self-management. The initial session (T0) covers disease-specific knowledge and rehabilitation strategies. The second session (T1) focuses on optimal inhaler use, and the final session (T2) introduces advanced airway clearance techniques, building on prior learning. The curriculum progresses incrementally, tailored to participants' learning abilities to gradually improve disease self-management. Additionally, at baseline, each patient will receive disease education manuals for home study.

#### 2.7.2 Training sessions

The intervention group will participate in three instructor-led training sessions focused on respiratory optimization. The initial session (T0) will provide personalized instruction in breathing techniques (pursed-lip and diaphragmatic breathing) and physical exercises (air cycling exercises, hip bridge exercises, seated stretching, standing stretching, and lower limb stretching), as illustrated in Figure 2. Subsequent sessions (T1 and T2) will concentrate on refining techniques, correcting errors, and optimizing performance. Additionally, participants will adhere to a home-based exercise regimen prescribed for 5 days each week.

**Figure 2 F2:**
[figure not shown]
Training exercises included in the program. **(A)** Air cycling exercises; **(B)** hip bridge exercises; **(C)** seated stretching; **(D)** standing stretching; **(E)** lower limb stretching.

#### 2.7.3 Harmonica sessions

Participants in the intervention group will receive three progressive harmonica lessons (T0, T2, T3), conducted by professional music instructors, designed to optimize skill development. The initial lesson (T0) will cover harmonica fundamentals, including instrument anatomy, maintenance and cleaning, harmonica-based breathing techniques, and basic performance skills, establishing a foundation for subsequent lessons. At baseline, simple songs will be selected to build patients' confidence. Participants will be provided with structured written materials outlining practice methods and musical exercises. Subsequent lessons (T2 and T3) will introduce classical songs of increasing difficulty, building on foundational skills and progressively enhancing technical proficiency and enjoyment. Throughout the six-month intervention, participants will engage in a daily 30-min continuous (no-break) practice of a specified set of songs.

#### 2.7.4 Tele-supervision and guidance for intervention group

Upon randomization, a WeChat group will be established for each intervention cohort, including participants themselves, their family members (if they choose), a home-training supervisor and recorder, a rehabilitation instructor, and a harmonica instructor. For participants with limited device familiarity or access, one-on-one personalized WeChat training will be conducted at baseline, including video tutorials, content uploads, and interaction with PR staff. Family members will be trained if needed to assist with remote monitoring.

Participants will upload daily videos of their training and harmonica playing, report training duration, and complete rehabilitation training diaries documenting exercise and harmonica practice times. The supervisor and recorder will independently review the videos to verify adherence, and discrepancies will be resolved through double-checking the video recordings. Additionally, the supervisor and recorder will send daily reminders, track attendance, and note any absences. Rehabilitation and harmonica instructors will conduct real-time video assessments of participants' techniques, providing immediate feedback, personalized guidance, and addressing participant queries.

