### 2.3 Eligibility and sample size

Eligible patients must have a clinical diagnosis of COPD and a post-bronchodilator forced expiratory volume in one second (FEV_1_) to forced vital capacity (FVC) ratio of < 70%. Exclusion criteria include recent COPD exacerbations (within 6 weeks), resting oxygen saturation (SpO_2_) below 88% on room air or inadequate oxygenation despite supplementation; as well as severe dyspnea with Modified Medical Research Council (mMRC) grade 4, recent myocardial infarction, unstable angina, severe arrhythmias (e.g., ventricular arrhythmias or rapid atrial fibrillation), or pulmonary hypertension with right heart failure. Additional exclusions include comorbidities affecting physical activity (e.g., neurological disorders, cancer, significant musculoskeletal issues), cognitive impairments, and inability to communicate in Chinese. Furthermore, those with prior participation in PR within 6 months, or regular experience playing harmonica or similar wind instruments, are excluded to ensure baseline equivalence, minimize learning and behavioral biases, and avoid psychological effects, thereby enhancing the validity and reliability of the study outcomes.

Based on an anticipated minimum clinically important difference (MCID) of a 4% increase in percent predicted FEV_1_ (FEV_1_%) and a standard deviation of 10% (16), each group will require 99 participants to achieve 80% power at a 0.05 two-tailed significance level. Considering a 20% dropout rate, the study plans to enroll 248 patients (124 per group) (17).

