#### 2.8.1 Supervision and guidance for control group

After randomization, control group participants will be added to a dedicated WeChat group comprising participants, their family members (optional), a home-training recorder and supervisor, and a rehabilitation instructor. The same recording methods and daily prompts will be applied as in the intervention group. The home-training supervisor will review uploaded videos, monitor adherence, send daily reminders, and track training completion. The rehabilitation instructor will conduct real-time video assessments to ensure proper adherence to the training protocols.

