### 2.10 Statistical analysis

Data will be collected using a dual-entry and verification process, incorporating range checks, logic tests, and source document validation to ensure data integrity (37). All analyses will be conducted with R software version 4.4.0. The primary analysis will follow the intention-to-treat principle (ITT), including all randomized participants in their assigned groups (38). Baseline characteristics will be summarized using descriptive statistics, with continuous variables compared using independent *t*-tests and categorical variables using chi-square tests between the harmonica-integrated PR group and the standard PR care group. Primary and secondary outcomes will be analyzed using mixed-effects models to account for the repeated measures design (39). Sensitivity analyses will include per-protocol analyses focusing on participants who fully adhered to the intervention. Effect sizes and 95% confidence intervals will be reported alongside *p*-values. All statistical tests will be two-tailed, with significance set at *p* < 0.05. Subgroup analyses will be conducted based on pre-specified baseline characteristics as necessary. Cohen's D will be used as the effect size metric, with common thresholds (small: 0.2, medium: 0.5, large: 0.8) (40).

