## 3 Discussion

By leveraging the respiratory benefits of harmonica playing—which simulates respiratory training and incorporates the advantages of music therapy—along with the convenience of home-based training and the instant support of tele-supervision, this study aims to evaluate the effectiveness of a harmonica-integrated, tele-supervised home-based PR program. This innovative approach may offer an accessible, affordable, and enjoyable non-pharmacological treatment option for patients with COPD.

With a robust sample size of 248 participants, a six-month intervention, standardized protocols, and comprehensive outcome measures, the study enhances statistical power, generalizability, and long-term assessment (41, 42). Key design features include a partially blinded methodology, where care providers, outcome assessors, and data analysts are unaware of group assignments, minimizing bias and ensuring objective evaluation (43). The home-based approach improves accessibility for remote or mobility-limited patients, reduces travel and costs, and may lower infection risks compared to clinic settings (44, 45). Tele-supervision involves roles such as home-training recorder, supervisor, and instructors, providing real-time guidance and technique correction. Communication via WeChat fosters a supportive community, while video recordings ensure objective adherence data (46). Harmonica training progresses from basic music theory and breathing techniques to advanced playing skills, promoting mastery and enjoyment. Concurrently, comprehensive PR sessions include breathing exercises (e.g., pursed-lip, diaphragmatic) and physical activities (e.g., air cycling, hip bridge, resistance band stretching) to enhance respiratory and overall muscle function (41, 47). Regular technical assessments and introductory guidance support effective home-based training.

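### Participants are supervised in WeChat groups nested within arm, but the sample size and the stated purpose of the mixed model treat them as independent apart from repeated measures

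*Protocol article*

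**What the plan says.** Allocation is by individual, 1:1 (Protocol article, 2.5). Delivery after randomisation is in groups.

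- **Intervention arm (2.7.4):** "a WeChat group will be established for each intervention cohort". Besides participants and optional family members, the group holds a supervisor, a recorder, a rehabilitation instructor and a harmonica instructor. Table 1 adds that "Instructors will select songs of gradually increasing difficulty, providing hands-on teaching for each song and offering personalized guidance".
- **Control arm (2.8.1):** "control group participants will be added to a dedicated WeChat group", with a recorder, a supervisor and a rehabilitation instructor. The wording is singular; cohorts are not mentioned.
- **Expected role of the group (section 3):** "Communication via WeChat fosters a supportive community".
- **Sample size (2.3):** based on "a 4% increase in percent predicted FEV_1_ (FEV_1_%) and a standard deviation of 10" per cent, "each group will require 99 participants to achieve 80% power at a 0.05 two-tailed significance level". Then: "Considering a 20% dropout rate, the study plans to enroll 248 patients (124 per group". No ICC or design effect appears.
- **Analysis (2.10):** "Primary and secondary outcomes will be analyzed using mixed-effects models to account for the repeated measures design". No term for WeChat group, cohort or instructor is named.

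The limitations in section 3 do not mention clustering or operator effects. The article does not give the number or size of the groups, or say whether the same staff serve both arms.

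**The concern.** Members of one WeChat group share staff, reminders and peer contact for six months. If that makes their outcomes more alike, they are not independent observations. A model with participant-level random effects only would then give standard errors that are too small, and p < 0.05 would be reached too often.

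The outcomes most open to this are perceived social support (MSPSS), HADS, adherence and satisfaction, because peer contact and staff encouragement act on them directly. FEV1% is less exposed.

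A second problem concerns the contrast itself. If controls sit in one group, that group's effect is part of the control mean. If staff also differ by arm, so does the skill of the people delivering the rehabilitation components that section 2.8 says are the same in both arms.

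**Working it through.** **Inputs from the article (2.3):** difference 4 points of FEV1%, SD 10, two-sided alpha 0.05, power 80%, 99 per group, 20% dropout, 248 enrolled.

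**Assumed, because the article gives neither:** m = 10 or 20 participants per WeChat group in both arms; ICC = 0, 0.01, 0.02 or 0.05.

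**Step 1: reproduce the plan's figure.** n per group = 2 × (1.960 + 0.842)² × 10² / 4² = 98.1, rounded up to 99. Enrolment: 99 / 0.8 = 123.75, rounded up to 124 per group, 248 in total. Power at 99 per group = Φ(4 / (10 × √(2/99)) − 1.96) = Φ(2.814 − 1.96) = 0.80. The stated numbers reproduce exactly for independent participants, so they contain no allowance for clustering.

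**Step 2: groups of equal size in both arms.**

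- Design effect: DE = 1 + (m − 1) × ICC
- True two-sided error of the unadjusted test: 2 × [1 − Φ(1.96 / √DE)]
- Power at 99 per group: Φ(2.814 / √DE − 1.96)
- Enrolment to restore 80%: 98.1 × DE per group, rounded up, divided by 0.8, rounded up, times 2

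| m | ICC | DE | True error | Power | Enrolment for 80% |
|---|---|---|---|---|---|
| any | 0 | 1.00 | 5.0% | 80% | 248 |
| 10 | 0.01 | 1.09 | 6.0% | 77% | 268 |
| 10 | 0.02 | 1.18 | 7.1% | 74% | 290 |
| 10 | 0.05 | 1.45 | 10.4% | 65% | 358 |
| 20 | 0.01 | 1.19 | 7.2% | 73% | 294 |
| 20 | 0.02 | 1.38 | 9.5% | 67% | 340 |
| 20 | 0.05 | 1.95 | 16.0% | 52% | 480 |

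Example, m = 20 and ICC 0.05: DE = 1 + 19 × 0.05 = 1.95, √DE = 1.40, 1.96 / 1.40 = 1.40 gives an error of 16%, and 2.814 / 1.40 − 1.96 = 0.05 gives power of 52%.

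The error column depends only on m and ICC, so it applies to any outcome with that ICC. The power and enrolment columns are for FEV1% only. These are normal approximations without correction for a small number of groups.

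**Step 3: one control group.** Assume 99 controls in one group and 99 intervention participants in 5 groups. Variance of the difference = 100 × [2(1 − ICC)/99 + ICC × (1 + 1/5)], against 200/99 = 2.02 unadjusted. For ICC 0.01 this is 100 × (0.0200 + 0.0120) = 3.20, and √(3.20 / 2.02) = 1.26. The true standard error is 1.26, 1.47 and 1.98 times the unadjusted one at ICC 0.01, 0.02 and 0.05.

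**Step 4: clustering in the intervention arm only.** With 5 groups, variance = 100 × [2(1 − ICC)/99 + ICC/5 + ICC/99]. The factors are 1.05, 1.09 and 1.21.

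**The case against.** The strongest reply is that the article condenses a fuller plan. Section 2.10 names a purpose for the mixed model but lists no random effects and excludes none, so an analysis plan that is not shown could contain a group term. That stands, and the absence of such a term here is not by itself an error. It does not cover the sample size, which 2.3 fixes without a design effect, or the way groups are formed, which 2.7.4 and 2.8.1 describe and no later model can change.

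Second, the ICC for FEV1% may be close to zero. It is a spirometric measure taken by blinded assessors, training is mostly at home, and feedback is personalised. Section 2.7.3 also refers to written materials and a set list of songs, which limits how far instructors diverge. This stands too, and is why the range starts at an ICC of 0.

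Third, a reader might infer that each arm has its own instructors and supervisors, so that a better instructor would show up as a harmonica effect. The article does not say so. It lists roles for each group, not separate people. Section 2.6, under which staff know only the treatment they give, is compatible with separate staff but does not state it. Section 2.8, which gives both arms the same rehabilitation sessions, is compatible with shared staff. Operator confounding is therefore a possibility to be settled.

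**Conclusion.** The point holds in conditional form. Delivery is in WeChat groups nested within arm, while the sample size and the stated purpose of the model treat participants as independent apart from repeated measures. Under the assumed range, the consequence runs from none (ICC 0) to a true error of 16% and power of 52% (groups of 20, ICC 0.05).

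It would go too far to say that the intervals are certainly too narrow or that the primary result is compromised: this needs an ICC above zero and group sizes that the article does not give. The concern is stronger for MSPSS, HADS, adherence and satisfaction than for FEV1%.

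The step 2 figures do not describe a single control group, which is how 2.8.1 reads. In that case, or where staff differ by arm, no model can separate the group or operator effect from the arm effect. Several groups and staff sets per arm would at least let that variation be estimated and carried into the standard error.

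**What to change.** 1. In 2.7.4 and 2.8.1, state the number and size of WeChat groups per arm and whether staff cross arms. Record WeChat group and instructor or supervisor ID for every participant.
2. Form control WeChat groups by enrolment cohort, as in the intervention arm, so that each arm has several.
3. In 2.10, add a random intercept for WeChat group to the primary and secondary models, with participant nested in group and small-sample degrees of freedom.
4. In 2.3, state that the 80% power assumes no clustering, and give the power at an assumed ICC.
5. If only one control group is used, apply the group term to the intervention arm only (a partially nested model) and state the confounding of group and operator with arm as a limitation.

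Rotating the same staff through both arms would reduce operator confounding, but staff who review videos from both would see which groups play the harmonica. It should not be adopted unless reconciled with the blinding in 2.6.

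**Cost:** ID fields, several control groups in place of one, and one model term. Intervals become somewhat wider and the stated power less favourable. Restoring 80% power by enrolment would take the numbers in the last column of the table; reporting the power at the planned 248 needs no extra patients. IDs are easy to record during delivery and hard to reconstruct afterwards.
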